## E. Objectives, Specific Aims and Rationale

### *Objective and aims:*

The overall objective is to inform public health policy by providing timely evidence on how key individual-level demographic characteristics and comorbidities affect excess mortality risk over time during the course of the COVID-19 pandemic.

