#### K. Planned use of linked data (if applicable):

Additional analyses will be completed when set 19 of the linkage data is released, assuming that ONS linked data coverage will then include the pandemic period. We request access to linked ONS mortality data so that analyses can be repeated using ONS certified death as the outcome and linked HES admitted patient care data to improve ascertainment of ethnicity and comorbidities for stratification in later analyses.

Linked practice level Carstairs quintiles are requested to allow stratification by area-based deprivation in the initial analyses using primary care data only. We also request urban rural data as COVID-19 infections and mortality will be affected by deprivation, population density and distance from hospital. **Patient level Carstairs quintiles are requested for the linked analysis.**

Risk of identification of practice or patient location will be mitigated by restricting users who have access to the raw CPRD and linked data to [name] and [name] who understand the increased risk of identification with these data and have completed mandatory data protection training at LSHTM. This will be implemented by password protecting folders where data are stored in accordance with LSHTM IT policy. Patient and practice identifiers will be pseudonymised in datasets released to other investigators.

Analyses using linked data will be restricted to English practices and patients who are eligible for linkage, and to the time periods of linked data coverage.

**This study will use demographic/clinical and death data available in CPRD primary care and linked data sources to examine how pre-existing illnesses (e.g. respiratory disease, heart disease, diabetes) and risk factors such as BMI and smoking are associated with excess mortality risk during the course of the COVID-19 pandemic in the UK. The findings will provide key information to inform clinical guidance, resource planning and policies for protecting the most vulnerable people in the UK, including in England and Wales, during the pandemic.**

[figure not shown]

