#### **N. Exposures, Outcomes and Covariates**

The main exposure of interest is the Covid-19 pandemic starting from 1st March 2020.

The main outcome is mortality, identified from primary care data using the CPRD derived death date. In secondary analyses we will use updated linked ONS mortality data when available to repeat the analysis using the ONS death date.

Covariates of interest for stratification are:

- Geographical region
- Age (initial time series counts to be generated in 5 year categories, then collapsed further for analysis)
- Sex
- Smoking status (current, never, ex)
- BMI group (WHO groupings)
- Ethnicity (White, South Asian, Black, Mixed Other)
- Number of individuals in a household (CPRD GOLD only)
- Care home residency (CPRD GOLD only)
- History of comorbidities including those relevant to government “vulnerable groups” policy\*:
  - o Asthma
  - o Chronic respiratory disease (other than asthma)
  - o Cardiovascular disease
  - o Diabetes
  - o Cancer
  - o Chronic liver disease
  - o Chronic neurological diseases
  - o Chronic kidney disease
  - o Organ transplant recipients
  - o Problems with spleen
  - o On immunosuppressive drugs
  - o Hypertension
  - o Autoimmune disease
  - o Endocrine disease (including thyroid others)
  - o Multimorbidity

We will use code lists and definitions developed by the LSHTM Health Protection Research Unit on Immunisation where available, and where needed develop new code lists using systematic dictionary keyword searches, manual review, and clinical sign-off; these will be published online and linked in research outputs.

\*Current UK government guidance on who should be considered vulnerable has been largely based on policies developed for previous epidemic respiratory viruses, notably influenza. Understanding of Covid-19 risk factors is improving rapidly. We will submit a protocol amendment should new Covid-19 risk factors that can be measured using the available data emerge during the study.

[figure not shown]

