### 1) Primary analysis - time series approach

We will derive weekly counts of numbers of deaths in contributing practices (see section L “Study Population”) from the start of the study period to the end of the study period. Population denominator sizes (number under active follow-up) will also be extracted. We will extract these counts overall, and stratified by age, sex, region and other factors (see section N “Covariates”). Where these factors are time-varying, counts will reflect changes over time.

We will fit generalised linear models with a negative binomial error structure to model the counts of deaths, taking account of variable denominator sizes [approach we took in Matthews et al media and statins paper to deal with variable denominators, BMJ2016]. The model will initially include the outcome (mortality), exposure (2020 pandemic period vs pre-pandemic), age, sex, interactions between the exposure and age and sex, Fourier terms (a harmonic function of calendar week) to capture seasonality, a continuous function of calendar year (linear, or higher order polynomial if evidence of non-linearity) to capture any underlying trends, and if relevant dummy indicators to capture extreme flu seasons. When investigating excess mortality within subgroups, further exposure covariate stratification factors will be added individually, and in combinations where there is sufficient information. Interactions between the exposure and stratification factors will provide estimates of the relative effect of the pandemic in strata.

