**P. Plan for addressing confounding**

This is not a hypothesis testing/causal modelling study, so confounding per se is not an issue. The role of covariates will be explored by stratification in the main analyses and by adjustment and stratification in the exploratory individual cohort analyses.

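### No pandemic × region term is committed to when other factors are studied, so interactions for regionally clustered factors may partly reflect place

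*Protocol*

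**What the plan says.** Section O, subsection 1, sets out an initial negative binomial model with the pandemic indicator, age, sex, "interactions between the exposure and age and sex, Fourier terms (a harmonic function of calendar week) to capture seasonality", a calendar-year trend and, if relevant, indicators for extreme flu seasons. For subgroups it continues: "When investigating excess mortality within subgroups, further exposure covariate stratification factors will be added individually", "and in combinations where there is sufficient information". The output is then defined: "Interactions between the exposure and stratification factors will provide estimates of the relative effect of the pandemic in strata".

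Four other places bear on this:

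- Section N lists "Geographical region" as one stratification factor among many. Section O extracts the weekly counts by region, so a region term can be fitted.
- Section J wants both databases so that joint associations can be explored with mutually adjusted models. It does not say which factors those models contain.
- Section K justifies requesting area-level data because "COVID-19 infections and mortality will be affected by deprivation, population density and distance from hospital".
- Section P states: "This is not a hypothesis testing/causal modelling study, so confounding per se is not an issue".

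**The concern.** Comparing a group with itself before and during the pandemic removes stable differences in its baseline mortality. It does not remove differences in how hard the epidemic hit the places where the group lives. If the pandemic rate ratio varies by region and a factor is unevenly distributed across regions, a model without pandemic × region passes some of the regional contrast to the pandemic × factor term. The sign can go either way: a factor concentrated in lightly affected regions would look protective.

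The plan already lets age and sex modify the pandemic effect in every model, so it accepts the principle. It names place as a driver in Section K, yet makes no matching commitment in Section O.

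The interaction is the main output of Aim 2. The overall objective in Section E is to show "how key individual-level demographic characteristics and comorbidities affect excess mortality risk over time", for use in public health policy. A reader who takes the interaction as a property of the person, when part of it belongs to the place, could aim protection at the wrong target.

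**Working it through.** **The plan's own precision.** Section J reports a simulated pandemic IRR of 1.89 (1.74–2.07) and a comorbidity interaction of 1.97 (1.85–2.08), with true values of 2.0 for both. The simulation cannot be rerun, because its denominators, baseline rates and dispersion are not given. No regional variation is mentioned in it. The intervals imply:

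- Pandemic: SE of log IRR = ln(2.07/1.74)/(2 × 1.96) = 0.044.
- Interaction: SE = ln(2.08/1.85)/(2 × 1.96) = 0.030.
- Interaction half-width: exp(1.96 × 0.0299) = 1.06, or about 6%.

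At that precision, an estimated interaction above about 1.06 has a 95% interval that excludes 1.

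**Interaction produced by place alone.** Suppose the factor has no true effect on the pandemic rate ratio. Let RH and RL be the pandemic rate ratios in hard-hit and other regions. Let sF and s0 be the shares of baseline expected deaths (after age and sex) that fall in hard-hit regions, for people with and without the factor. Then

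interaction = [sF·RH + (1 − sF)·RL] / [s0·RH + (1 − s0)·RL].

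None of these four inputs is in the documents; all are assumed. With s0 = 10%:

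| RH / RL | sF 10% | sF 15% | sF 30% | sF 50% | sF 60% |
|---|---|---|---|---|---|
| 1.5 / 1.25 | 1.00 | 1.01 | 1.04 | 1.08 | 1.10 |
| 2.0 / 1.5 | 1.00 | 1.02 | 1.06 | 1.13 | 1.16 |
| 2.0 / 1.25 | 1.00 | 1.03 | 1.11 | 1.23 | 1.28 |
| 3.0 / 1.5 | 1.00 | 1.05 | 1.18 | 1.36 | 1.45 |

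Example, second row, sF 50%: (0.5 × 2.0 + 0.5 × 1.5)/(0.1 × 2.0 + 0.9 × 1.5) = 1.75/1.55 = 1.129.

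A second set of assumptions, with RL = 1.6:

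- 40% versus 10%: RH = 2.0 gives 1.76/1.64 = 1.07; RH = 2.5 gives 1.96/1.69 = 1.16.
- 30% versus 15%: RH = 2.0 gives 1.72/1.66 = 1.04; RH = 2.5 gives 1.87/1.735 = 1.08.

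**Check in a fitted model.** One hundred negative binomial weekly series were simulated over 322 weeks, with Fourier and trend terms, RH 2.0, RL 1.5, sF 50%, s0 10% and a true factor interaction of 1.0. The mean estimated interaction was:

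- 1.13 with counts aggregated over region (formula 1.129);
- 1.03 with region as a main effect only;
- 1.00 with region and pandemic × region.

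The middle figure should not be generalised. It comes from how the negative binomial variance weights the regional cells. Fitting the expected counts with Poisson weights and a region main effect leaves the interaction at 1.129. It is the pandemic × region term that removes the place component.

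**Effect of more data.** Section J's simulation used GOLD denominators. Section I gives median weekly deaths of 560 (GOLD) and 1657 (Aurum), and (560 + 1657)/560 = 3.96. If the SE scaled simply, it would fall to 0.0299/√3.96 = 0.015, and an interaction of about 1.03 would exclude 1. That is a best case, because practices in both databases are counted once and overdispersion need not scale. Pooling narrows the interval and leaves the place component where it was.

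**The case against.** The strongest reply is that the study is declared descriptive in Section G. A group's excess mortality, including the part due to where its members live, is a legitimate descriptive quantity. Section T leaves independent effects to the cohort approach and says that the time series cannot establish cause. This stands: the unadjusted interaction is not wrong as a description. It does not settle the matter, because the objective is worded in terms of effect and Section P gives no warning that factor and place may be mixed. The final section on changes to the approved protocol also says that the cohort analysis was not attempted. That reports later conduct and is no flaw in the plan as written, but the independent estimates were then not produced.

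A reader might infer that the plan only ever fits factors one at a time. It does not. Combinations and mutually adjusted models are provided for, each added factor receives its own pandemic interaction, and a factor-plus-region model falls within the written plan. What is missing is a commitment: the combinations are conditional, and none is tied to region.

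A reader might also infer that subgroup interactions will turn out to be artefacts of place. The documents do not support that. They give neither regional pandemic ratios nor the regional distribution of any factor, and for an evenly spread factor the distortion is nil.

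Two further points stand. Section K names deprivation, density and distance from hospital rather than region, and requests area-level measures, so region is only a partial proxy. Requiring the region terms in every model also has a price: Section J found 8% of cells with zero denominators, and the final section reports convergence problems from low numbers of deaths.

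**Conclusion.** The point holds as a gap in commitment. Pandemic × age and pandemic × sex are fixed; pandemic × region is not, although the plan itself expects place to matter and has the counts to fit the term. Interactions for regionally clustered factors may therefore partly reflect regional severity.

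Over the assumed contrasts in the main table, the place-only interaction is 1.00 with no clustering, 1.01–1.05 with weak clustering (15% versus 10%), and 1.08–1.45 with strong clustering (50–60% versus 10%). The benchmark is a half-width of about 6%, for one simulated comorbidity of cancer-like prevalence. Weakly clustered factors would stay below that benchmark, while strongly clustered ones would exceed it. Which factors fall where cannot be told from the documents. This is a cheap improvement in analysis and labelling. It is not a reason to discard the planned contrast.

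**What to change.** In Section O, subsection 1, state that each subgroup interaction will be reported twice: as planned, and with region and pandemic × region added, with regions collapsed where cells are sparse. Label the version without those terms as descriptive and unadjusted for place. In Section P, replace the opening statement with one saying that unadjusted interactions may mix the factor with the place where people live, and that the paired results show how much they change.

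The counts are already to be extracted by region, so no new data are needed. The costs are somewhat wider intervals (the amount was not calculated), possible collapsing of regions for rare conditions, and possible non-convergence for the rarest. Variation within regions remains, because region does not fully capture deprivation or population density. Reporting both versions avoids imposing the extra terms on every analysis and lets the reader separate factor from place as far as region allows.

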### 2) Secondary analysis - SMR-based approach

We will use the stratified weekly counts generated for the time series approach, and collapse years into two periods (all pre-pandemic vs 2020 pandemic). Age/sex/comorbidity-specific expected weekly death rates for the pandemic period will be generated using the pre-pandemic data, and compared with observed weekly deaths in the pandemic period. Risk factors will be analysed one at a time, and combined where numbers allow. Standardised mortality ratios will be calculated as observed / expected and 95% confidence intervals will be generated from a saturated Poisson model.

### 3) Secondary analysis - Cohort approach

Using data from March 1st 2014 to the end of the study period, we will fit a proportional hazards model for time to death on an underlying age timescale (with extensions if proportionality of the hazards assumption is not met). Individuals will enter the analysis 1 year after entry into CPRD to allow classification of comorbidities. Time-updated calendar month and year will be included in the model, alongside a time-updated indicator for the pandemic period, and individual-level covariates. Interactions between the pandemic indicator and covariates will be added one at a time initially and in combinations, where possible, to describe differences in excess mortality between risk factor groups.

#### Validation of approaches / data

We will compare estimates of all cause excess age/sex-specific mortality over time by week during the course of the COVID-19 pandemic with similar estimates derived from national death registration data.

[figure not shown]

**P. Plan for addressing confounding**

This is not a hypothesis testing/causal modelling study, so confounding per se is not an issue. The role of covariates will be explored by stratification in the main analyses and by adjustment and stratification in the exploratory individual cohort analyses.

**Q. Plans for addressing missing data**

Analyses stratified by BMI, smoking and ethnicity are likely to have missing data. In our primary analyses, we will create binary yes/no variables for obesity, ever smoked, white ethnicity assuming that individuals with missing data are not obese, have never smoked and are white. We will conduct sensitivity analyses restricted to the study population with data available, with appropriate assessment of possible selection bias affecting the results. We will also conduct sensitivity analyses whereby missing obesity, smoking and ethnicity data are randomly recoded as taking any value other than the reference to assess the impact of misclassification bias.

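### Section Q recodes missing BMI, smoking and ethnicity to one extreme or the other, which usually attenuates the pandemic-by-factor interaction and does not in general bound it; its binary coding is not reconciled with Section N

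*Protocol*

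**What the plan says.** Section Q expects missing data for BMI, smoking and ethnicity. For the primary analyses it states that "we will create binary yes/no variables for obesity, ever smoked, white ethnicity". Anyone without a record goes into the reference group of each variable: the plan proceeds "assuming that individuals with missing data are not obese, have never smoked and are white". It then plans two sensitivity analyses:

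- Recorded data only: "We will conduct sensitivity analyses restricted to the study population with data available", with an assessment of selection bias.
- Recoding: missing values are "randomly recoded as taking any value other than the reference to assess the impact of misclassification bias".

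Section N lists the same three factors, for stratification, with several levels each: "Smoking status (current, never, ex"; "BMI group (WHO groupings"; "Ethnicity (White, South Asian, Black, Mixed Other". For age, Section N says that categories will be collapsed later. It says nothing of the kind for these three, and Section Q does not refer back to Section N.

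The quantity at stake is the interaction between the pandemic indicator and the factor (Section O, primary analysis). Section C adds that absolute as well as relative differences will be described.

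**The concern.** The primary rule places people whose true status is exposed but unrecorded in the reference group. The recode does the reverse and places people whose true status is reference in the exposed group. Each makes the two compared groups more alike in ordinary circumstances. Setting one beside the other then shows how far two biased estimates differ, which does not tell the reader where the truth lies.

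There is also a problem of wording. A yes/no variable has only one value other than the reference, so the random element in the recode has nothing to act on unless a different coding is intended.

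Finally, the binary coding cannot separate South Asian from Black patients, current from ex-smokers, or underweight from normal BMI. How excess mortality varies by demographic and lifestyle characteristics is primary aim 2 in Section E, and the stated purpose is to inform policy.

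**Working it through.** The protocol gives no figure for missing data, so there is nothing of its own to reproduce. The check asks what each recoding would estimate on average.

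**Inputs.** All are assumptions unless marked: true ratio of pandemic IRRs R = 1.5; factor prevalence p and missing share m as in the table; missingness unrelated to true status or to death; equal baseline mortality.

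**Missing set to reference (primary).** The truly exposed share of the group coded reference is c = m·p / [(1−m)(1−p) + m]. The expected ratio is R / [(1−c) + c·R].

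**Missing set to non-reference (recode).** The truly unexposed share of the group coded exposed is c₂ = m(1−p) / [(1−m)p + m]. The expected ratio is c₂ + (1−c₂)·R.

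Worked case, ethnicity with p = 0.14 and m = 0.20:

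- c = 0.028/0.888 = 0.032, so the primary gives 1.5/(0.968 + 0.047) = 1.48.
- c₂ = 0.172/0.312 = 0.551, so the recode gives 0.551 + 0.449 × 1.5 = 1.22.

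| Factor | p | m | Primary | Recode | Share of recoded exposed group truly unexposed |
|---|---|---|---|---|---|
| Non-white | 0.14 | 0.20 | 1.48 | 1.22 | 55% |
| Non-white | 0.14 | 0.40 | 1.46 | 1.14 | 71% |
| Obese | 0.28 | 0.15 | 1.46 | 1.36 | 28% |
| Obese | 0.28 | 0.30 | 1.43 | 1.28 | 44% |
| Ever smoked | 0.50 | 0.05 | 1.47 | 1.48 | 5% |
| Ever smoked | 0.50 | 0.15 | 1.41 | 1.43 | 13% |

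Every entry is below 1.5. Restriction to recorded data gives 1.5 in this setting.

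**A second scale, from the protocol's own simulation.** Section J simulates a doubling of death rates that is twice as severe in people with a comorbidity: IRR 2 in the unexposed, 4 in the exposed, interaction 2.00. With assumed p = 0.30 and m = 0.20, the primary rule gives 1.85, the recode 1.68 and recorded data 2.00. Over p from 0.15 to 0.60 and m from 0.10 to 0.30, the ranges are 1.53 to 1.97 (primary) and 1.37 to 1.94 (recode). Attenuation also holds in two variants:

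- Missingness depends on true status: with 10% of exposed and 30% of unexposed missing, 1.92 and 1.59; with the shares reversed, 1.80 and 1.81.
- A protective interaction of 0.50 (p = 0.30, m = 0.20): 0.52 and 0.66.

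**Where attenuation fails.** Both recodings attenuate as long as the missing group's overall pandemic rate ratio lies between those of the recorded unexposed and exposed. With p = 0.30, the missing group's ratio is 0.3 × 4 + 0.7 × 2 = 2.6 when its members respond like recorded people of the same status. Now change only that group's ratio (m = 0.20, equal baseline mortality):

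- ×0.6, so 1.56, below the recorded range of 2 to 4: primary 2.12, recode 1.45.
- ×1.6, so 4.16, above that range: primary 1.56, recode 2.04.

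In both cases the pair brackets 2.00, and in the first the primary exaggerates.

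The absolute scale can differ as well. Take a baseline of 10 deaths per 1000, halved in people with missing data, with their rate ratios unchanged. The true difference in excess deaths is 18.0 per 1000. The primary gives 20.5, the recode 10.0 and recorded data 20.0.

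**The case against.** The strongest defence is that Section Q does not rest on the two recodings. It also plans the recorded-data analysis, which is unbiased for the interaction in the setting where both recodings attenuate, and Section K plans linked hospital data to improve ascertainment of ethnicity. That stands, and it lowers the severity.

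Several stronger readings are tempting but not supported:

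- **That both recodings always dilute, so the truth always lies outside the pair.** The counter-examples above show otherwise, and the protocol gives nothing on mortality in people with missing data to settle which case applies.
- **That the protocol claims to bracket the truth.** It does not. It says only that the recode assesses misclassification.
- **That the two recodings would agree and so reassure falsely.** For ethnicity (1.46 to 1.48 against 1.14 to 1.22) and obesity (1.43 to 1.46 against 1.28 to 1.36) they visibly disagree. Only smoking agrees closely, and there the error is modest.
- **That the primary estimate is badly wrong.** In the 1.5 illustration it is about 2% to 6% low (1.48/1.5 to 1.41/1.5). The large distortions belong to the recode.
- **That Section Q flatly contradicts Section N.** Section N lists stratifiers, Section J foresees some collapsing of sparse strata, and Section T speaks of people with and without individual risk factors. This is an unreconciled specification.

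The random recode might also be meant for Section N's multi-level categories, since Section Q ties binary coding to the primary analyses. The wording allows that. Even so, no missing person would remain in the reference group, so the non-reference groups would still absorb people who truly belong to it, and the result would not be on the same coding as the primary.

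**Conclusion.** The point holds in conditional form. When missingness is unrelated to death given true status, both single-value recodings attenuate the relative interaction and neither bounds it. Outside that case the direction depends on unreported mortality in people with missing data, so a reader cannot tell from the two recodings which way the primary estimate errs. The sizes quoted rest on assumed prevalences, missing shares and effects.

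Two parts need no such assumption: the recode is degenerate if the binary coding is kept, and Sections N and Q give different categories for the same factors. Given the modest primary bias in the 1.5 illustration and the recorded-data analysis already planned, this is a should-fix.

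**What to change.** 1. Use Section N's categories for smoking, BMI and ethnicity, collapsing only where cells are too sparse, and state in Section Q how its coding relates to Section N.
2. Show people with no record as their own stratum, with their own death rate and pandemic IRR. Report the planned recorded-data estimate beside the missing-as-reference estimate with equal prominence. The stratum's IRR indicates which of the cases above applies.
3. Replace the all-to-non-reference recode with multiple imputation, or with draws from the recorded distribution by age, sex, region and vital status.

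The cost is revised wording in Section Q, sparser cells, and some imputation code applied to individual records before the weekly counts are formed. Recorded-data estimates remain open to selection bias, which Section Q already plans to assess; the absolute-scale example (20.0 against 18.0) shows why that assessment is still needed.
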